### 2.3. Sample Size

The current study is a phase 2 preliminary clinical study, thus we will recruit 45 patients without sample size calculations. Fifteen patients will be assigned to each of the three intervention groups. The results from this study will be used to calculate the sample size for further confirmatory clinical trials.

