### 2.7. Intervention

Based on the syndrome differentiation diagnosis, three different herbal medications will be prescribed to each patient for up to 12 weeks. Among the patients with fatigue, the pattern/syndrome of lung-spleen qi deficiency group will be administered Bojungikgi-tang (CV1, Kracie Bojungikgitang Extract Fine Granule, Kolmar Pharma, Korea), and the syndrome of dual deficiency of qi and yin group will be administered Kyungok-go (CV2, Kyungbang Kyungokgo, KBPharm, Korea). The cognitive dysfunction group will be administered Cheonwangbosim-dan (CV3, Soonsimhwan, Hanpoong Pharm, Korea). Bojungikgi-tang (CV1) will be administered one sachet (3.75 g) twice a day before or in between meals. Kyungok-go (CV2) will be administered one sachet (20 g) twice a day in the morning and evening before or in between meals. Cheonwangbosim-dan (CV3) will be administered one sachet (one dose) once a day in between meals. The evaluation for the continuation of herbal medicine administration will be conducted at visits 2 and 3. If visual analog scale (VAS, 0–100) for fatigue or cognitive dysfunction at the current visit is improved by <50% of VAS at the previous visit, and the patients want to take herbal medicine, the same herbal medicine as previously prescribed will be re-administered for 4 weeks. For this evaluation, the symptom improvement rate at the current visit (VAS score of the current visit/VAS score of the previous visit (%)) and whether the patients want to continue the administration of herbal medicines will be investigated.

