### 2.8. Outcomes

#### 2.8.1. Primary Outcome

As the primary outcome, the treatment success rate after herbal medications for up to 12 weeks for fatigue and cognitive dysfunction in patients who have recovered from COVID-19 will be evaluated. VAS (0–100) for fatigue or cognitive dysfunction before (visit 1) and after administration of herbal medicines (visit 4) will be assessed. If VAS is >15 points, it is defined as treatment success. The frequency or ratio of treatment success patients will be presented, based on the fatigue and cognitive dysfunction groups, respectively.

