### 2.12. Statistical Analysis

For assessing the feasibility of this study design, we will analyze the subject recruitment rate, dropout rate, and dropout reasons. The subject recruitment rate will be calculated by dividing the total number of study subjects by the total number of participants screened (%). The dropout rate will be calculated for all participants and each herbal medication group. The dropout reasons will also be assessed. For continuous variables that will be assessed to evaluate the potential clinical effectiveness of herbal medications, the standard deviation, median, minimum, and maximum values for each time point will be presented. An analysis of covariance (ANCOVA) test will be conducted for differences between herbal medication groups (*p* < 0.05). If the assumption of ANCOVA is tested and the basic assumptions such as normality and equal variance of data are violated, the Kruskal–Wallis test will be performed. Statistical analysis will be conducted using the R-software (R 4.1.2, The R Foundation, www.r-project.org, accessed on 9 August 2022) or Jamovi software (Version 1.8.0, The jamovi project, www.jamovi.org, accessed on 9 August 2022). A full analysis set will be used to analyze variables for effectiveness evaluation. Data on safety evaluation will be used with the safety set. All statistical tests, unless otherwise defined, are tested with the two-sided test, with a 5% significance level.

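### The primary fatigue success rate merges two products, CV1 and CV2, although patients are recruited per herb and the results are meant to size later trials

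*Protocol article*

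**What the plan says.** - **Reporting unit of the primary outcome** (protocol article, section 2.8.1): "The frequency or ratio of treatment success patients will be presented, based on the fatigue and cognitive dysfunction groups, respectively". That makes two rates, one per symptom group.
- **What each symptom group contains** (section 2.7). Within fatigue, "the pattern/syndrome of lung-spleen qi deficiency group will be administered Bojungikgi-tang" (CV1) and "the syndrome of dual deficiency of qi and yin group will be administered Kyungok-go" (CV2). For the other symptom, "The cognitive dysfunction group will be administered Cheonwangbosim-dan" (CV3). Table 2 gives CV1 and CV2 different patterns and different diagnostic signs.
- **Recruitment unit** (section 2.3): "we will recruit 45 patients without sample size calculations", and "Fifteen patients will be assigned to each of the three intervention groups".
- **Use of the results** (section 2.3): "The results from this study will be used to calculate the sample size for further confirmatory clinical trials".
- **Other outcomes.** Adherence, recruitment and dropout are reported by herb or intervention group (sections 2.8.2 and 2.12).
- **Effectiveness test** (section 2.12): an ANCOVA "test will be conducted for differences between herbal medication groups", with Kruskal–Wallis as fallback. SD, median, minimum and maximum are planned at each time point.
- **Allocation** (section 2.6): no control group and no randomisation. The herb follows from the main symptom and then the syndrome pattern.

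**The concern.** The primary outcome is the one place where the plan leaves the herb as its unit. In the cognitive group this changes nothing, because only CV3 is given. In the fatigue group it averages two products prescribed to two kinds of patient. If one product is followed by many successes and the other by few, the planned figure shows a middling rate that describes neither. It also depends on how many patients happen to fall into each pattern.

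This matters because of the use stated in section 2.3. Whoever plans a later trial of Bojungikgi-tang or of Kyungok-go would start from a rate belonging to neither. The effectiveness test is by herb but cannot replace the missing rates: with the herb determined by symptom and syndrome, a difference between groups may reflect the product, the patients or both.

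**Working it through.** **Plan's own figure.** 3 herbs × 15 = 45, which agrees with section 2.3. The fatigue group is then 15 + 15 = 30 and the cognitive group 15. The article gives no power, precision, success rate or SD, so there is nothing further to reproduce.

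**Assumptions.** All success counts and rates below are illustrative, as is the 40% comparator rate in step 3. None comes from the article.

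**Step 1: what a pooled rate hides.** The exact (Clopper–Pearson) 95% limits for x successes in n are the 0.025 quantile of Beta(x, n − x + 1) and the 0.975 quantile of Beta(x + 1, n − x). The pooled result is 18/30 = 60% (40.6 to 77.3%) in every row.

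| CV1 | CV2 |
|---|---|
| 9/15 = 60% (32.3 to 83.7%) | 9/15 = 60% (32.3 to 83.7%) |
| 12/15 = 80% (51.9 to 95.7%) | 6/15 = 40% (16.3 to 67.7%) |
| 14/15 = 93% (68.1 to 99.8%) | 4/15 = 27% (7.8 to 55.1%) |

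**Step 2: dependence on the mix.** Pooled rate = (n1·p1 + n2·p2)/(n1 + n2). With p1 = 0.80 and p2 = 0.40:
- 15:15 gives (12 + 6)/30 = 60%
- 20:10 gives (16 + 4)/30 = 66.7%
- 10:20 gives (8 + 8)/30 = 53.3%

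The equal split is planned. If recruitment by pattern departs from it, the pooled rate moves although neither herb's rate has changed.

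**Step 3: consequence for a later trial of one herb.** Two-sided 5%, 80% power, two proportions:

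n per arm = [1.96·√(2·p̄·(1 − p̄)) + 0.8416·√(p1(1 − p1) + p2(1 − p2))]² / (p1 − p2)²

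- Pooled 60% against 40%: (1.3859 + 0.5831)²/0.04 = 96.9, so 97 per arm.
- A herb at 80% against 40%: (1.3579 + 0.5323)²/0.16 = 22.3, so 23 per arm.
- A herb at 40% against 40%: no difference to detect.

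**Step 4: precision per herb.** Exact interval widths at n = 15 are 67.7 − 16.3 = 51.4 points at 6/15, 78.7 − 26.6 = 52.1 at 8/15, 83.7 − 32.3 = 51.4 at 9/15, and 95.7 − 51.9 = 43.8 at 12/15. That is about 44 to 52 points.

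**Step 5: SD of change.** Var(change) = s₀² + s₄² − 2·r·s₀·s₄, where s₀ and s₄ are the SDs at baseline and visit 4 and r is the within-patient correlation. SDs by time point do not give r, so the SD of change has to be reported directly. For normal data an SD from 15 patients has 95% limits of √(14/26.12) = 0.73 and √(14/5.63) = 1.58 times the estimate: imprecise, but usable for planning if shown with its uncertainty.

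**Step 6: the between-herb test.** CV3 differs from CV1 and CV2 in the presenting symptom, and CV1 differs from CV2 in the syndrome pattern (section 2.6, Table 2). Because the pattern determines the herb, no pattern is treated with two herbs. Covariate adjustment therefore has no overlap from which to separate product from patient type.

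**The case against.** The best defence is that reporting by symptom is coherent. The objective in section 2.1 is worded by symptom, section 2.6 allocates first by symptom, and the VAS is symptom-specific. The fatigue rate then describes pattern-matched herbal treatment of fatigue. Section 2.3 does not say that each later trial will test a single herb, and nothing in section 2.8.1 forbids a breakdown by herb. This stands as a reason to keep the pooled rate. It is not a reason to make it the only one, because recruitment and the other reported outcomes are by herb.

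Three stronger readings are tempting, and the article does not support them:

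- *The trial fails to provide what the next trial needs.* This goes too far. SDs by time point and per-herb dropout, recruitment and adherence are planning inputs, and the CV3 success rate is already specific to one product.
- *Omitting confidence intervals, tables of change or a rule for missing visit 4 values is an error.* A condensed article commonly leaves these to the full protocol or analysis plan, neither of which is shown. Section 2.8.1 does assess VAS before and after treatment. Intervals and change are therefore requested here, not counted as faults.
- *The primary outcome compares fatigue with cognition.* It does not. The two rates are presented side by side with no test between them.

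It is also fair to object that within-herb change is not a treatment effect. Without a control it mixes any product effect with natural recovery and regression to the mean, the more so as entry requires a CIS total above 76. That stands, and it limits how the change may be described.

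**Conclusion.** The point holds in limited form. Section 2.8.1 makes a stated choice that merges CV1 and CV2 in the primary rate, at odds with recruitment per herb and of little help for sizing a trial of either product. The cognitive rate is unaffected.

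The possible size is large: on the assumed figures, one pooled 60% covers herb rates from 60/60 to 93/27, and planning on it gives 97 per arm where 23 would do for a herb at 80%. These figures illustrate what could be hidden and do not predict what will be found. If the two herbs have similar rates, little is lost.

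The between-herb test cannot attribute a difference to the product. This follows from the allocation rule and needs no numerical assumption. The remedy is a change of presentation. The design and the data collection can stay as they are.

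**What to change.** 1. In section 2.8.1, present the primary success proportion for CV1, CV2 and CV3 separately, each with an exact 95% CI. Keep the pooled fatigue rate as a supplement, with the CV1 and CV2 numbers behind it.
2. Report the within-herb change in VAS from baseline to visit 4 with mean, SD and 95% CI, described as change under treatment and not as a treatment effect. Settle the baseline visit first: section 2.8.1 names visit 1, while Table 1 lists the VAS at visit 0 and not at visit 1.
3. In section 2.12, label the between-herb tests descriptive and say that herb cannot be separated from symptom and syndrome.

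Cost: a few tables from data already collected, with no extra patients or visits. The drawback is that the per-herb intervals will be wide, as step 4 of the working shows. Anyone sizing the next trial should see that uncertainty.

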#### 2.8.2. Secondary Outcome

##### Medication Adherence

Medication adherence will be monitored by counting the number of returned and taken medications at each visit. In the case of the number of returned drugs and number of taken drugs being unmatched with the number of prescribed drugs, the reason for this shall be recorded in the case report form. Medication adherence is calculated as follows:$$Medication\;adherence\;\left(\%\right)=\frac{The\;number\;of\;taken\;drugs}{The\;number\;of\;prescribed\;drugs\;in\;the\;duration\;*}\times 100$$
* The number of prescribed drugs in the duration means the number of drugs should be taken from the time of initial administration to before the time of returning the untaken drugs.

The final medication adherence will be evaluated at 12 weeks after the initial administration (visit 4 or end point of medication), and the sum of the number of taken herbal medicines divided by the sum of the number of prescribed herbal medicines in the duration will be calculated and collected at visits 2, 3, and 4. Mean, standard deviation, median, minimum, and maximum value of the final medication adherences (%) for all study patients will be represented for each herbal medicine group, and multiple comparison analyses will be conducted among groups.

##### Checklist Individual Strength (CIS)

CIS is an indicator for evaluating fatigue in the last 2 weeks, and will be accessed by patients themselves using a questionnaire as instructed by the principal investigator or other researchers at visits 2, 3, 4, 5, and 6. Each patient will answer the CIS questionnaire after receiving sufficient explanation about its purpose and method from the clinical investigator [5]. The total CIS score will be compared among the intervention groups for each visit.

##### Chalder Fatigue Scale (ChFS) and Subscale

The ChFS will be evaluated by using the numeric rating scale 100 (range 0–100) mm following the Korean version of ChFS. The total score and subscale for physical- (No. 1–7) and mental health (No. 8–11) will be recorded at visits 2, 3, 4, 5, and 6 [6]. The total score and subscale scores will be calculated and compared among groups for each visit.

##### EQ-5D-5L

EQ-5D is a standardized measure of health-related quality of life. EQ-5D classifies the health state profile as five levels in five dimensions. The five dimensions are mobility, self-care, usual activity, pain/discomfort, and anxiety/depression. The five levels in each dimension are classified as: (1) no problems, (2) slight problems, (3) moderate problems, (4) severe problems, and (5) unable to (mobility, self-care, usual activities), extreme (pain/depression) or extremely (anxious/depressed). EQ-5D scores will be calculated at visits 2, 3,4, 5 and 6, and compared among groups for each visit.

##### Pittsburgh Sleep Quality Index (PSQI)-K

The PSQI-K is a self-reported questionnaire for evaluating sleep quality that consists of questionnaires assessing seven components about sleep quality including subjective sleep quality, sleep latency, sleep duration, habitual sleep efficiency, sleep disturbances, use of sleeping medication, and daytime dysfunction. The global score is calculated by the sum of the score ranging from 0 to 21. Global scores will be assessed at visits 2, 3, 4, 5, and 6 and compared among groups for each visit.

##### Korean-Montreal Cognitive Assessment (K-MoCA)

The K-MoCA is a simple cognitive function assessment tool and is more sensitive than a mini-mental state exam (MMSE) in assessing cognitive decline. K-MoCA consists of visuospatial/executive (5 points), naming (3 points), attention (6 points), language (3 points), abstraction (2 points), orientation (6 points) and delayed recall (5 points). The maximum score is 30 points, and the normal range is >23 points [7]. Total scores will be calculated at visits 2, 3,4, 5, and 6 and compared among groups for each visit.

##### Cognitive Failure Questionnaire (CFQ)

The CFQ is an evaluation tool for cognitive function by measuring slip and error of perception, memory, and motor functioning in daily life, consisting of 25 individual items, and each item is evaluated by frequency of mistakes, rating from 0 (never) to 4 (very often). The total score is calculated by the sum of the rating of 25 items, yielding a score from 0–100. Forgetfulness, distractibility, and false triggering can be assessed through CFQ. CFQ will be assessed at visit 6, and compared among multiple groups [8].

##### Beck’s Depression Inventory (BDI)

BDI will be assessed to evaluate depression and its severity after COVID-19 or recovery. BDI consists of 21 items in four domains of cognitive, emotional, motivational, and physical symptoms of depression. Each item is rated on a scale of 0 to 3, and the total score of the items is ranged 0–63 points, with higher scores indicating more severe symptoms of depression. BDI will be assessed at visits 2, 3, 4, 5, and 6, and compared among multiple groups [9].

##### Digit Span Test in Korean-Wechsler Adult Intelligence Scale (WAIS)

The WAIS, the most widely used intelligence test tool in clinical practice, is used to measure cognitive impairment changes in cognitive dysfunction. The digit span test, a subset of WAIS, is a well-validated and convenient tool to measure verbal short-term memory and working memory capacity. It consists of digits forward (DF) and digits backward (DB) components, which require patients to repeat a series of spoken digits in either forward (usually 3–9 digits) or reverse order (2–8 digits), respectively. In case of false response in a row, the test is discontinued. The DF score is the number of digits of the largest number correctly spoken by the patient, and the DB score is the number of digits of the largest number correctly repeated by the patient. A score of DF, DB, and DF minus DB is calculated. Higher DF and DB scores indicate better short-term memory. In cases of DF minus DB scores of >5 points, the working memory is determined as abnormal. The digit span test will be assessed at visits 4, 5, and 6, and compared among multiple groups [10].

##### Korean-Boston Naming Test-15 (K-BNT-15)

The BNT is widely used to determine changes in language proficiency based on cognitive impairments, a validated test for visual confrontation naming abilities. The 60-item version of BNT contains a 60-line drawing of objects to naming response, and requires 15–30 min to test. The BNT-15 is the shortened version of BNT and simplified to test the administration and scoring process in a short time [11]. In the current study, the Korean version of BNT-15 will be used to examine language function changes based on cognitive dysfunction [12]. For this test, “Dragon”, “Tadpole”, “Cobweb”, “Snowman”, “Boots”, “Turtle Ship”, “Icicle”, “Camel”, “Thimble”, “Extinguisher”, “Mermaid”, “Dinosaur”, “Stroller”, “Toshi (armband)”, and “Starfish” are shown in sequence and, if it is the correct answer, rates 1 point; otherwise, it rates 0 points. Total score is added up to calculate the K-BNT-15 score. The K-BNT-15 test will be assessed at visits 4, 5, and 6, and compared among multiple groups.

##### Analysis of Patient Recruitment Rate, Enrolment Rate, Dropout Rate, and Reasons for Dropout for Feasibility Evaluation

The patient recruitment rate is calculated by the ratio (total, each intervention group) of recruited patients during the study period to planned study patients (45 patients, 15 patients per each intervention group). The patient enrolment rate is calculated by dividing the total number of study patients by the total number of screening patients. Reasons for dropout will be documented, and the dropout rate is calculated and will be compared for all study patients and each intervention group.

##### Analysis of Immune Responses and Metabolites

The effects of herbal medicine after recovery from COVID-19 on immune responses and metabolites related to fatigue and cognitive dysfunction will be investigated by peripheral blood-immunologic and metabolomic analysis. The patient’s peripheral blood will be collected, 25 mL at visits 0, 4, 5, and 6. To explore the effects related to the immune response, the following experiments will be conducted:Single-cell RNA sequencing (scRNA-seq) for immune related gene expressions.Flowcytometric analysis for immunophenotyping SARS-CoV-2-specific T cell response.Quantitative analysis for inflammatory cytokines, and chemokines in serum sample.Quantitative analysis for SARS-CoV-2 antigens (spike or nucleoprotein), specific antibodies (IgG, IgM, or IgA), and neutralizing antibodies in serum samples.

Furthermore, to investigate the changes caused by herbal medicine in metabolites related to fatigue and cognitive dysfunction after recovery from COVID-19, a metabolomic analysis based on mass spectrometry will be conducted using serum sample. In the present study, using gas chromatography–mass spectrometry and liquid chromatography–mass spectrometry, metabolic changes caused by herbal medicine will be investigated using metabolite profile analysis including primary and secondary metabolites, such as alkaloids and derivatives, benzenoids, homogeneous non-metal compounds, lipids and lipid-like molecules, nucleosides, nucleotides, and analogs, organic acids and derivatives, organic nitrogen compounds, organic oxygen compounds, organo-halogen compounds, organo-heterocyclic compounds, phenylpropanoids and polyketides.

### 2.9. Safety Evaluation

For safety evaluation, adverse events, vital signs, laboratory tests, and electrocardiograms will be evaluated. Adverse events refer to all harmful and unintended symptoms or signs, including abnormal results in laboratory tests, or diseases that occurred in patients administered herbal medicine that do not necessarily have to be a causal relationship. Vital signs including blood pressure, body temperature, breathing, and heart rate, will be recorded at every visit. Electrocardiography will be performed to monitor the presence of severe heart disease, such as acute myocardial infarction and ventricular fibrillation. Laboratory tests will determine the red blood cell, hemoglobin, hematocrit, platelet, white blood cell, fasting blood sugar, BUN, creatinine, AST, ALT, and blood electrolyte (Na, K, Cl) levels, and the observed values and changes from the baseline value will be evaluated.

### 2.10. Adverse Event Reporting

The information on adverse events occurring in study patients shall be voluntarily reported by the patients or their representatives immediately, and should be confirmed through clinical examinations and interviews by the principal investigator or other researchers. The investigation for adverse events includes the date of onset and disappearance, the severity, medical measures or treatments, the causality with herbal medicine, and the progression.

#### 2.10.1. Assessment of Subjective and Objective Symptoms

The subjective and objective symptoms by adverse reaction will be investigated through medical examination by the investigator, and the severity of symptoms will be recorded following the evaluation criteria. The causality between adverse events and herbal medicine will be also evaluated.

#### 2.10.2. Assessment of Measured Tests Such as Laboratory Tests and Vital Signs

Clinically significant abnormal changes in test results, such as laboratory tests and vital signs, will be followed up until symptom improvement. Moreover, interference factors for the test will be recorded through the interview.

